#### Exposures

Two distinct types of neighborhood exposures will be created (Table 2): (1) residential neighborhood variables around participants’ homes [25-27] and (2) GPS activity space (ie, places where participants travel throughout the day) [25-27]. Each type of measure will be linked to accelerometer data with respective time and measured intensity of PA levels (Figure 2; Table 2). Both residential and GPS activity space measures will include neighborhood poverty (eg, neighborhood deprivation index from US census [62,63]), physical disorder (by virtual neighborhood audits [41,64]), police-reported crime (from DC databases [65,72]), and the modified retail food environment index (defined as the ratio of healthy to unhealthy food stores) [73]. In addition, parks, gyms, and recreation facilities will be used to create the count and density of these PA facilities to better understand how participants engage in PA [67]. As a measure of feasibility and practicality, we used 11 participants from a protocol (ClinicalTrials.gov identifier NCT03288207) to create residential buffers around participants’ homes (ie, circular [25-27] and line-based road network buffers; Figure 3 [74]) and GPS activity space buffers based on SD ellipses [66,75] (Figure 4) and individuals’ daily paths (Figure 5) [66]. Figures 2-5 were based on hypothetical data to show each different buffer and buffer type (actual study participant data are not shown). Some points occurring around residential areas will be weighted.

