### Statistical Analysis

To test aim 1 hypothesis, we will first test the differences in stress-related neural activity by Wards 3 and 5. Subsequently, we will examine associations between each neighborhood social environment variable based on residential and GPS-derived measures as well as EMA measures separately and stress-related neural activity, adjusting for all covariates. Covariates will include sociodemographic variables (eg, age, race [White or Black adults], and individual-level income) and health-related variables (eg, PA). Each model will be assessed based on the value of the Akaike information criterion (AIC) to select the most parsimonious model. Third (sub-aim 1), after determining a statistically significant neighborhood exposure variable, we will test for an interaction between the specific neighborhood exposure variable and objectively measured PA and psychosocial factors (a potential moderator). If the interaction term is significant, we will stratify the association by high or low objectively measured PA based on the mean and by high or low psychosocial factors (eg, perceived stress scale scores) based on the mean.

To test aim 2 hypothesis, we will first test the differences in the measures of vascular inflammation and function (Table 2) by Wards 3 and 5. Second, we will examine associations between each neighborhood social environment variable based on residential and GPS-derived measures as well as EMA separately and each vascular measure, adjusting for all covariates. The same covariates will be used as in aim 1. Each model will be assessed based on the value of the AIC to select the best-fit model. Third (sub-aim 2), after we identify a statistically significant exposure variable, we will test for an interaction between the specific exposure variable and objectively measured PA and psychosocial factors. If the interaction term is significant, we will then stratify the association by high or low objectively measured PA based on the mean and by high or low psychosocial factors (eg, perceived stress scale scores) based on the mean.

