**Participant’s residence (county, Maryland or Ward, Washington, DC), n (%)**			
	Prince George’s County	6 (54)	
	Ward 5	3 (27)	
	Ward 7	2 (18)	

Mean areas varied by the size of the buffers (200 m, 400 m, and 800 m) and types of buffers based on residential (circular and line-based road network buffers) and GPS activity space (Table 5). As expected, the areas for a line-based road network buffer were smaller than that for a circular buffer. Areas for residential buffers (circular and network buffers) were also smaller than the GPS activity space areas. We plan to explore different sizes and types of buffers.

**Table 5 table5:** Mean areas for participants’ residential (circular and network) and GPS activity space buffers (N=11).

Type of buffer	Size (km^2^), mean (SD)		
	200 m	400 m	800 m
Circular buffer	0.13 (0)	0.50 (0)	2.01 (0)
Network buffer^a^	0.05 (0.02)	0.17 (0.08)	0.64 (0.33)
GPS activity space	20.48 (8.09)	53.32 (20.77)	123.02 (46.72)

^a^On the basis of a line-based road network buffer around the residence of a participant.

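### Aims 1 and 2 screen many separate exposure models for significance with no primary exposure or buffer named, and the AIC step can conflict with the stated covariate adjustment

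*Protocol article*

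**What the plan says.** The Objectives section words each aim and sub-aim as the test of a hypothesis. For aims 1 and 2 the Statistical Analysis section sets out a sequence:

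1. Compare the outcome between Wards 3 and 5.
2. Fit separate exposure models: "we will examine associations between each neighborhood social environment variable based on residential and GPS-derived measures as well as EMA measures separately", adjusted for the full covariate list, which names individual-level income.
3. Apply AIC: "Each model will be assessed based on the value of the Akaike information criterion (AIC) to select the most parsimonious model".
4. Move to the sub-aim "after determining a statistically significant neighborhood exposure variable" (aim 1). For aim 2, "after we identify a statistically significant exposure variable, we will test for an interaction". A significant interaction leads to stratification at the mean.

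Aim 3 follows steps 1 to 3 but has no sub-aim and no significance gate.

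On the number of exposures, the Exposures section says "Two distinct types of neighborhood exposures will be created", residential and GPS activity space. It continues: "Both residential and GPS activity space measures will include neighborhood poverty", followed by physical disorder, crime and the retail food index. Facility counts are listed in addition.

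On buffers, the feasibility results report that "Mean areas varied by the size of the buffers (200 m, 400 m, and 800 m) and types of buffers", and close with "We plan to explore different sizes and types of buffers". No size or type is fixed for the main study.

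**The concern.** The plan describes a selection procedure. Several exposures are each tested against the same outcome, and the ones that pass a significance screen decide what sub-aims 1 and 2 examine. With no primary exposure or buffer, the chance that something passes by luck exceeds the level of any single test, and the reader has no pre-named result against which to judge it. A chance association could then be followed by interaction tests and subgroup estimates in about 60 women.

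The AIC step raises a second problem. Adjusting every model for the full covariate list and then choosing the most parsimonious model cannot both hold if the choice is among covariate sets. The Background section criticises an earlier study of neighborhood SES and amygdala activity because it did not account for individual-level SES. A rule that allows individual income to drop out could bring back that weakness.

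**Working it through.** **The plan's own figure.** The article gives no alpha and no familywise error rate. Its only statistical figure is the precision of the SD of amygdala FDG with 30 per group. The chi-square bound is sqrt((n−1)/χ²₀.₁₀(n−1)) = 1.21 at n = 30, which agrees with the stated 20%. That figure does not bear on the error rate of the exposure models.

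**Number of models per outcome.**
- Fixed by the Exposures section: 4 constructs × 2 bases = 8.
- If every definition in Table 5 is carried over: 3 circular + 3 network + 3 GPS = 9 definitions, and 4 × 9 = 36.
- EMA measures and facility counts come on top of both.

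**Chance of at least one false positive per outcome, independent models.** Assume a two-sided 0.05 for each model and no true association: 1 − 0.95^m.
- m = 8: 1 − 0.95^8 = 0.34
- m = 36: 1 − 0.95^36 = 0.84

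**Correlated models.** Exposures overlap, and buffers around one home are nested, so independence overstates the error. Null regressions were simulated with 60 women, 4 covariates and 8,000 runs per setting. The correlations are assumptions, since the article gives none.

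| Correlation within / between constructs | 8 models | 36 models |
|---|---|---|
| 0.5 / 0.3 | 0.28 | 0.66 |
| 0.8 / 0.3 | 0.26 | 0.49 |
| 0.7 / 0.5 | 0.24 | 0.48 |
| 0.9 / 0.5 | 0.21 | 0.34 |
| 0.95 / 0.7 | 0.16 | 0.23 |
| 0.95 / 0.9 | 0.12 | 0.16 |

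With zero correlation the simulation gives 0.34 and 0.84, matching the formula. The smallest entry, 0.12, is still more than twice 0.05.

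**Aim 2 as a whole.** Table 2 lists three vascular measures (arterial inflammation, pulse wave velocity, augmentation index), and none is primary. That makes 3 × 8 = 24 models, and 1 − 0.95^24 = 0.71 if independent. Correlation would lower this.

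**AIC, two readings.**
- *AIC ranks exposures or buffers.* Among models of equal size fitted to the same women, the lowest AIC belongs to the smallest p-value. The error is the one already computed, and AIC adds nothing to it.
- *AIC chooses covariates.* A one-parameter covariate stays only if its likelihood-ratio statistic exceeds 2, and P(χ²₁ > 2) = 0.157. For an assumed partial correlation r between income and the outcome, take a noncentral χ²₁ with noncentrality 60·r²/(1−r²). At r = 0.15 the noncentrality is 1.38 and income is dropped with probability 0.59. At r = 0.20 it is 2.50 and the probability is 0.43. Both values of r are illustrative; the article gives none.

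**The case against.** The strongest reply is that this is a pilot. The Limitations section says its intent is feasibility and sample-size needs, the Expectations section calls aim 3 hypothesis-generating, and an article may leave multiplicity control to an SAP that is not shown. This stands in part. Silence on a correction is not itself a fault, and aim 3 needs no error control. It does not answer the written screen-then-test sequence for aims 1 and 2, which are framed as hypothesis tests.

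The count can also be argued down. The Background section illustrates the neighborhood social environment by poverty, social disorder and crime. Without the food index there are 3 × 2 = 6 models, and 1 − 0.95^6 = 0.26 if independent. The conclusion is the same.

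A reader might infer several stronger points that the article does not support:
- *That 36 models is a minimum.* The nine buffer definitions come from feasibility work in 11 women. The main study says only that sizes and types will be explored.
- *That a chance finding is likely.* Among the correlated settings tried, the per-outcome figure passes one half only for 36 models at the weakest correlation.
- *That any significant exposure establishes the aim.* No decision rule is given, and the ward comparison comes first.
- *That the AIC values are not comparable because GPS and EMA models use fewer women.* The Devices section defines a valid day but not an analysis set.
- *That the larger study would be powered on an inflated exposure association.* The Sample Size Calculation section refers to differences in biological measures and the SD of amygdala FDG, not to selected exposure coefficients.

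On AIC, a reading in which it compares only exposures or buffers is available and avoids the covariate conflict. The text does not say which models compete, so the conflict is conditional.

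**Conclusion.** The point holds for aims 1 and 2 in this limited form. The plan screens about 8 exposure models per outcome before EMA, with the upper end left open by the buffers, and lets significance choose the exposure for the sub-aims. At an assumed 0.05 per model, the chance of at least one false positive per outcome is 0.12 to 0.34 for 8 models, and 0.16 to 0.84 if all 36 are run. The lower ends rest on assumed strong correlation between exposures, the upper ends on independence. All lie well above the nominal level.

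The AIC wording is a separate, conditional defect. If AIC selects covariates, it contradicts the full adjustment and can remove individual income. The pilot purpose limits the consequences but does not remove the need to say which result tests each hypothesis.

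**What to change.** - For each of aims 1 and 2, name as primary either the ward contrast or one exposure in one stated buffer. For aim 2, also name one primary vascular outcome.
- Label all other exposure, buffer and outcome models, and all of aim 3, as exploratory. Report them as estimates with confidence intervals; false-discovery control is optional.
- Test the sub-aim interactions on the pre-named exposure, whether or not its main association is significant.
- Fix the covariate set in advance and always keep individual income. Limit AIC to comparing buffer definitions fitted to the same women.

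The cost is a few sentences of wording and no new data. The downside is that fewer secondary associations can be called significant.

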## Introduction

### Background

Promoting physical activity (PA) is a critical public health goal because insufficient PA participation affects all age groups and various racial and ethnic groups in the United States (US) [1]. Approximately 10% of deaths are attributed to insufficient PA in the US [2], and engaging in regular PA (ie, meeting the PA guidelines of at least 150 min/week of at least moderate intensity PA) can reduce the risk of numerous chronic diseases (eg, cardiovascular disease [CVD]) [3]. Furthermore, in 2018, the newly released Physical Activity Guidelines for Americans, 2nd edition documented that regular PA has immediate health benefits, including lowering blood pressure, increasing sleep quality, decreasing anxiety, and improving cognitive function and insulin sensitivity [4]. Despite the well-demonstrated PA benefits, most US adults do not engage in sufficient PA, when measured by accelerometers [5,6]. In particular, African American adults have a lower PA level than their White counterparts, with 7.7% of African American adults and 8.2% of White adults meeting the PA guidelines [6].

The application of a multilevel social-ecological framework to determine changes in the environment and policy that would promote PA participation has been supported by authoritative US health institutions and international organizations over the past two decades [7-9]. This conceptual framework identifies relevant factors at multiple levels, ranging from genetic, intrapersonal, interpersonal, social, and cultural, to environmental factors [10]. The key principle of the social-ecological model posits that each level can impact behavior, and individuals can impact and are influenced by their environment, particularly when considering psychosocial effects [11]. Recent interventions are increasingly focusing on the role that the neighborhood social environment (eg, poverty, social disorder, and crime [12]) may play as a source of stressors that shape low levels of PA at the population level [8,13].

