Although the neighborhood social environment is an important factor in promoting PA [13], a key limitation in neighborhood social environment research is that the majority of such research systematically focuses on residential areas (ie, home) when investigating relationships between objectively measured environmental exposures via geographic information system (GIS) and PA [13]. However, individuals are generally mobile and engage in daily activities that are not restricted to places close to residential areas (eg, workplace) [14]. This generates a geospatial mismatch between exposures to the neighborhood social environment and locations where health behaviors occur [13,15,16]. Previous studies have also used self-reported PA, resulting in potential recall and social desirability bias [17].

When coupled with the neighborhood social environment as a source of stressors, psychosocial factors, such as chronic stress and depression, have an inverse relationship with PA and ultimately CVD [18]. Furthermore, a recent study in adults without CVD and our research in African American women in Washington, DC, demonstrated that amygdala activity (ie, chronic stress–related neural activity) assessed via 18-fluorodeoxyglucose (FDG) positron emission tomography-computed tomography (PET/CT) were significantly associated with subsequent CVD events [19] and vascular inflammation, a subclinical marker of atherosclerosis [20,21]. In addition, another recent study showed that neighborhood-level socioeconomic status (SES) was inversely associated with amygdala activity and arterial inflammation [22]. These findings are important for validating the relationship between chronic stress because of neighborhood factors and CVD events. However, the major limitations of the previous study were that they did not account for individual-level SES in the analytic models. Instead, they used neighborhood-level SES as a proxy for individual-level SES and examined the associations between neighborhood SES and amygdala activity. Furthermore, participants were chosen from a clinical database, which was not representative of the general US adults, and they were predominantly White adults [22]. Further research is needed to elucidate the associations between psychosocial factors, amygdala activity, and biological markers of adverse cardiac events in diverse populations and to assess both individual- and neighborhood-level SES.

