To test aim 3 hypothesis, we will first test the differences in immune cell activation, immune cell function, and biomarker-based immune activation (Table 2) by Wards 3 and 5. Second, we will examine associations between each neighborhood social environment variable based on residential and GPS-derived measures as well as EMA separately and the measures of immune system activation, adjusting for all covariates. The covariates are described in aim 1. Each generalized linear mixed model will be assessed based on the value of the AIC to select the best-fit model.

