#### Expectations

We anticipate that aim 1 will improve our current knowledge of the links between adverse neighborhood social environment features (eg, physical disorder) and stress-related neural activity (ie, amygdala activity), based on our prior experience demonstrating differences in amygdala activity between the DC-CHNA cohort and age- or sex-matched healthy volunteers [53]. Throughout this pilot study, we will disseminate the findings to the DC-CHOC members to gather input on the relevance of study findings to city practitioners and policy makers. These data will provide new insights into the role of the neighborhood social environment as a source of chronic psychosocial stress that can impact CV health.

In aim 2, we will be able to compare differences in vascular function between participants from Ward 3 (high-SES neighborhood) and Ward 5 (low-SES neighborhood). In addition, we will test the moderation effects of objectively measured PA using accelerometers because it is well known that PA influences vascular structure and function [76]. We expect that those living in adverse neighborhood social environments may have worse vascular function, which can be moderated by levels of PA. Those engaging in higher PA may have better vascular function, even if they reside in adverse neighborhood social environments.

In aim 3, we will be able to compare differences in immune activation between populations from two distinct neighborhood conditions (Wards 3 vs 5). We will also determine precise neighborhood social environment exposures within one’s residential and GPS activity spaces that relate to immune system activation, while adjusting for objective PA levels. On the basis of our previous data showing differences in inflammatory biomarkers between the DC-CHNA cohort and healthy volunteers [20], we expect that aim 3 will also be hypothesis-generating and will identify potential pathways involved in immune cell activation and function along the neural-hematopoietic-inflammatory axis, influenced by adverse environmental conditions.

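### The neighborhood-exposure models of aims 1-3 adjust for physical activity, which the protocol places downstream of the neighborhood, so they estimate an association net of activity that the aims do not name

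*Protocol article*

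**What the plan says.** Each aim is analysed in steps (Statistical Analysis). The first step compares Wards 3 and 5, with no covariates stated. The second fits models for each neighborhood exposure (residential, GPS-derived and EMA-based) adjusted for all covariates. For aim 1 these are given as "Covariates will include sociodemographic variables (eg, age, race [White or Black adults], and individual-level income) and health-related variables (eg, PA"). For aim 2, "The same covariates will be used as in aim 1". For aim 3, "The covariates are described in aim 1", and the Expectations section repeats the intention: "relate to immune system activation, while adjusting for objective PA levels". Models are then judged by AIC.

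For sub-aims 1 and 2, an interaction with PA is tested only for an exposure already found statistically significant.

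On how PA relates to the neighborhood, the Background says that the social environment "may play as a source of stressors that shape low levels of PA at the population level", and that "psychosocial factors, such as chronic stress and depression, have an inverse relationship with PA and ultimately CVD". The Expectations section, on aim 2, takes an effect of PA on vascular structure and function as established. The Objectives state aims 1-3 as associations of neighborhood conditions with neural activity, vascular function and immune activation. PA enters there only as a moderator in the sub-aims.

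**The concern.** If adverse neighborhoods lower PA and low PA worsens the outcome, PA carries part of the association that the aims ask about. Holding PA fixed removes that part. The coefficient then answers a different question: what remains of the neighborhood association among women with the same PA. The protocol does not say that this is the question for aims 1 and 2.

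Two things are at stake. First, a weak or null coefficient could be read as no neighborhood association when part of it has been adjusted away. Second, the significance gate passes the effect on, because an exposure whose association is reduced by the adjustment may never reach the moderation test, although moderation by PA is what sub-aims 1 and 2 are about.

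AIC adds an ambiguity. The text does not say whether PA is forced into the model. If it is not, PA may stay for some exposures and outcomes and drop out for others, so coefficients reported together would not all mean the same thing.

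**Working it through.** **The plan's own figure.** The only precision figure is the 90% upper bound on the SD with 30 per group, stated as 20% above the estimate (Sample Size Calculation). Check: √(29/19.77) = 1.211, about 21%, so it is reproduced. It does not bear on this point. The protocol gives no effect size, path coefficient, alpha or power for the exposure models.

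**What the text supports for each link.**

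| Link | Stated? |
|---|---|
| Neighborhood to lower PA | Yes, hedged and at population level (Background) |
| Stress inversely related to PA | Yes (Background) |
| PA to vascular outcomes | Yes (Expectations, aim 2) |
| PA to amygdala or immune outcomes | Not stated |

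**Model.** All variables are standardized, with E the adverse exposure and Y the adverse outcome:

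- PA = -a·E + error
- Y = c·E - b·PA + error

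The total association is T = c + ab. The PA-adjusted coefficient is c = T - ab, and the proportion lost is ab/T.

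**Numbers.** T = 0.40 and the paths are assumptions. Power is from simulation with n = 60, a two-sided 5% test and no other covariates; without PA it is about 90%.

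| Paths (-a, -b) | Adjusted value | Loss | Power with PA |
|---|---|---|---|
| -0.1, -0.1 | 0.40 - 0.01 = 0.39 | 2.5% | about 88% |
| -0.3, -0.3 | 0.40 - 0.09 = 0.31 | 22.5% | about 71% |
| -0.4, -0.4 | 0.40 - 0.16 = 0.24 | 40% | about 50% |

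If either path is zero, nothing is lost.

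**Variant 1: PA responds to the outcome.** This is possible for aim 1, given the stated inverse link between stress and PA. Let PA = -a·E - r·Y + error, with p = a + rT and q = aT + r. The adjusted coefficient is (T - pq)/(1 - p²).

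- a = r = 0.1: (0.40 - 0.0196)/(1 - 0.0196) = 0.39
- a = r = 0.3: (0.40 - 0.1764)/(1 - 0.1764) = 0.27

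The shift is again downward.

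**Variant 2: an unmeasured common cause of PA and outcome,** with effects g on PA and h on Y. The adjusted coefficient is c + gha/(1 - a²). With a = 0.3 and b = 0.2, c = 0.40 - 0.06 = 0.34. With gh = ±0.25 the added term is ±0.25 × 0.3/0.91 = ±0.082, so the adjusted value is 0.26 or 0.42. The second exceeds the total of 0.40. The direction is therefore likely but not assured.

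**The case against.** The strongest reply is that the text does not support the broad reading a reader might take from it, namely that every analysis is adjusted for PA and every estimate is biased toward zero. Most of this reply stands.

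- **Not every analysis.** The ward comparison that opens each aim has no stated adjustment, and the groups are to be matched on age, race and BMI. It is a direct test of living in a higher- or lower-SES area. It does not, however, estimate the residential, GPS or EMA exposure associations, and these are what lead to the sub-aims.
- **AIC may drop PA.** True, but AIC favors keeping a variable that predicts the outcome, which is when the adjustment matters most.
- **Bias depends on the target.** If an association net of PA is intended, as the Expectations section suggests for aim 3, adjusting for a mediator is not in itself a bias. That stands, and it is why the target must be stated.
- **The pathway is only partly asserted.** The neighborhood-to-PA statement is hedged, and an effect of PA on the outcome is claimed for vascular measures only.
- **PA may confound GPS exposures.** Activity space is recorded over the same 14 days as PA and includes the places where women exercise, so PA can help determine the exposure. Dropping PA from all models could then introduce confounding. This stands and limits the remedy.
- **Timing is not decisive.** The accelerometer is worn after the PET/CT and pulse wave velocity tests, which makes it a weak confounder measure for aims 1 and 2. But blood is drawn again at the second visit, PA is also surveyed, and later measurement does not prove mediation.
- **Two roles are not a contradiction.** An interaction model needs the PA main effect.

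The study is also a cross-sectional pilot that disclaims causal inference. That tempers the consequences, but it does not settle which association is to be reported.

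**Conclusion.** The point holds in limited form. The neighborhood-exposure models of aims 1-3 adjust for a variable that the protocol describes as shaped by neighborhood stressors and, for vascular outcomes, as influencing the outcome. Where PA is retained, they estimate an association net of PA, while the aims name an association without that condition. Under the protocol's implied signs the net value is smaller.

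The size cannot be derived from the documents. Over the assumed range, the loss runs from 2.5% (negligible) to 40% of a total of 0.40. The result rests on a linear model, an assumed total and assumed paths, and a strong enough shared cause could reverse the direction. The documents do not support a claim of certain bias toward zero or of no unadjusted analysis. For a pilot this is a correction worth making because it is cheap and it affects which exposures reach the moderation tests; it does not undermine the study.

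**What to change.** In the Statistical Analysis section:

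1. State that the target for aims 1-3 is the total association between neighborhood exposure and outcome.
2. For residential exposures, make the model with sociodemographic covariates and without PA primary. Report the PA-adjusted model as a labelled secondary analysis of the association net of PA.
3. For GPS activity-space exposures, where PA may also determine the exposure, report the models with and without PA side by side.
4. Base the gate to sub-aims 1 and 2 on the model without PA, and keep the PA main effect in the interaction models.
5. Bring the aim 3 sentence in the Expectations section into line.

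The cost is a few sentences and one extra model per exposure-outcome pair, on data already being collected. The drawback is a longer results table, with two coefficients to explain for each pair.

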**Moderators**			
	PA^l^ via accelerometer or survey	A minute-by-minute PA (A^m^), daily mean moderate-to-vigorous PA minutes (A), total PA minutes (A), active transportation PA, and leisure-time PA minutes [46] (S^n^)	
	Psychosocial factors via ecological momentary assessment	Perceived neighborhood social environment [68,69]; mood states [70], perceived stress [49], and daily hassles [71]	

^a^FDG: fluorodeoxyglucose.

^b^PET/CT: positron emission tomography-computed tomography.

^c^CCR2: C-C chemokine receptor type 2.

^d^TLR2: toll like receptor 2.

^e^TNF-α: tumor necrosis factor α

^f^IL-6: interleukin-6.

^g^IFN-α: interferon-α.

^h^MCP-1: monocyte chemoattractant protein-1.

^i^VEGF-A: vascular endothelia growth factor-A.

^j^IL-RA: receptor antagonist.

^k^TGF-β: transforming growth factor β.

^l^PA: physical activity.

^m^A: assessed by accelerometer.

^n^S: assessed by survey.

The outcomes for immune cell activation studies will be the proportion of each detected immune cell, their receptor expression, and platelet adhesion (eg, proportion of classical clusters of differentiation, such as CD14+CD16- monocytes of all monocytes, or proportion of natural killer cells of all CD45+ cells; Table 2). Immune cell function for purified and isolated monocytes and natural killer cells will also be determined for each participant. For instance, the ability of monocytes to perform chemotaxis, migrate toward the monocyte chemoattractant protein-1 gradient, will be determined based on a chemotaxis coefficient, as well as the activity of the inflammasome by measurement of interleukin (IL)-1β and IL-18 release by enzyme-linked immunosorbent assay upon appropriate stimulation. In biomarker profiling, plasma or serum levels of the proposed cytokines, chemokines, and stress-related neurotransmitters, and hormones will be measured as concentrations in pg/mL.

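### Sub-aims 1 and 2 describe a significant interaction by splitting continuous moderators at the sample mean, which discards information that the interaction model already gives (minor)

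*Protocol article*

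**What the plan says.** In the protocol article, Statistical Analysis, sub-aim 1 begins once a statistically significant neighborhood exposure has been found: "we will test for an interaction between the specific neighborhood exposure variable and objectively measured PA and psychosocial factors". The scale on which the moderator enters that test is not stated. If the interaction is significant, the follow-up is: "we will stratify the association by high or low objectively measured PA based on the mean and by high or low psychosocial factors". Perceived stress scale scores are the example given for the psychosocial side, also cut at the mean. Sub-aim 2 repeats the rule for the vascular measures: "we will then stratify the association by high or low objectively measured PA based on the mean".

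The moderators are measured on continuous scales. Table 2 lists "daily mean moderate-to-vigorous PA minutes" and total PA minutes among the accelerometer measures. The Limitations section gives the sample as about 60 women and describes the study as a step towards a larger one. No other way of describing a significant interaction is offered.

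**The concern.** A significant interaction says that the exposure association changes with the moderator. The fitted model then gives the association, with its uncertainty, at any level of PA or stress, and uses every woman to do so. The planned follow-up instead estimates the association separately in two groups formed at the sample mean. That treats all women on one side of the cut as alike and places near-identical women on either side of it in different groups. Each slope then rests on part of an already small sample.

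At stake is the description of the association in active or stressed women. The Expectations section hopes to show that higher PA goes with better vascular function even in adverse neighborhoods, and the high-PA group is where a reader would look for that. The cut is also set by this sample's mean, so high PA here need not mean the same thing in the larger study.

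**Working it through.** The plan gives no figure for this step, so there is none to reproduce. It also gives no SD, skewness or reliability for any moderator. Inputs from the document are the split rule and about 60 women. Everything else below is an assumption.

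**1. Precision at the same PA level.** Data sets of 60 women were simulated with three covariates. In each, the slope estimated in the high group was compared with the interaction-model slope evaluated at that group's mean PA. Variance ratio = (SE in high group / SE from model)².

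| Moderator | SE, high group | SE, model at same mean PA | Variance ratio |
|---|---|---|---|
| Log-normal, CV 0.5 | 0.235 | 0.206 | 1.30 |
| Log-normal, CV 0.75 | 0.252 | 0.225 | 1.25 |
| Log-normal, CV 1.0 | 0.265 | 0.232 | 1.30 |

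A separate run with a symmetric moderator (30/30 split) gave 1.26, so the loss does not depend on skew. Repeat runs with three or four covariates gave about 1.3 to 1.5, the upper end with four covariates and CV 1.0. A ratio of 1.3 to 1.5 means an SE larger by √1.3 = 1.14 to √1.5 = 1.22, that is, intervals about 14% to 22% wider.

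**2. Size of the high group.** For a symmetric moderator it is about 30 of 60. For a log-normal moderator, the share above the mean = Φ(−s/2), with s = √ln(1 + CV²):

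- CV 0.5: s = 0.472, share 40.7%, 60 × 0.407 = 24 women
- CV 0.75: s = 0.668, share 36.9%, 22 women
- CV 1.0: s = 0.833, share 33.9%, 20 women

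The Sample Size Calculation section plans about 90 recruits with 20% loss. If 90 × 0.8 = 72 women were analyzed, the range would be 72 × 0.407 = 29 to 72 × 0.339 = 24.

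**3. What a stratum estimate looks like.** For an assumed partial correlation of 0.3 with four covariates, the 95% CI is tanh(atanh(0.3) ± 1.96/√(m − 7)):

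- m = 60: 0.04 to 0.52
- m = 30: −0.10 to 0.62
- m = 24: −0.16 to 0.66
- m = 21: −0.21 to 0.68

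This shows how little one group can say alone. It is not the like-for-like comparison, because m = 60 here is the association over all women. Step 1 is the fair comparison.

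**The case against.** The strongest reply is that the split decides nothing. The interaction is tested first, that test is not said to use the split variable, and the groups are formed only if it is significant. This stands: the formal test of moderation does not rest on the strata, which is why the point is minor. For the same reason, a reader might infer that moderation would be concluded from a pattern of significance in the low group and not in the high one. The document plans no such comparison of stratum p-values.

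Other stronger readings also fail:

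- **Skew as the cause.** The documents do not show that any moderator is skewed. The Introduction's figure of about 8% of adults meeting the activity guideline is at most a hint for PA, and nothing supports skew for the perceived stress score.
- **Misclassification through skew.** Women are put in the wrong group because of measurement error at any cut. At an assumed reliability of 0.8, the overall share is 14.8% for a symmetric measure and 13.2% for a strongly skewed one (log-SD 1.0). Keeping the moderator continuous does not remove measurement error.
- **A two- to threefold variance penalty.** Ratios of 2.1 to 3.1 appear if the high-group slope is set against the model slope at the 75th percentile of PA. Under the same log-normal assumption, the high group's mean PA lies further out, so those are slopes at different PA levels.

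It is also fair to say that the study is a pilot with an acknowledged small sample, and that percentiles are as sample-specific as a mean. The second point is met by stating the actual moderator values.

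**Conclusion.** The point holds as a minor one about description and interpretation. Splitting continuous moderators at the sample mean is a less precise way to estimate the association in active or stressed women than reading it from the interaction model: about 1.3 to 1.5 times the variance at the same PA level. That size rests on simulation with 60 women, three or four covariates and an interaction linear in the moderator. It applies with or without skew. The fall to about 24 to 20 women in the high group depends on the assumed log-normal shape with CV 0.5 to 1.0. That the cut does not carry over to the larger study needs no distributional assumption.

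**What to change.** In both sub-aims, replace the mean split as follows:

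- Keep PA and the psychosocial scores continuous in the interaction test and in its follow-up, and say so.
- Report the interaction estimate with its 95% CI.
- Report the exposure association with 95% CI from the interaction model at a few pre-stated moderator values. Fixed minutes or scores carry over best to the larger study. If the 25th, 50th and 75th percentiles are used, give their actual values.
- Label any high and low groups shown as descriptive.

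The cost is analysis wording only, with no new data. The downside is that the interaction is assumed linear in the moderator, which should be checked with a plot.
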